#### Outcome measures

The main outcome measure is falls over the 12-month study period. A fall is defined as *'Unintentionally coming to rest on the ground, floor, or other lower level' *[27,28]. Falls will be recorded on a falls calendar, a method used successfully in previous falls prevention studies [27]. Each fall will be followed up with a telephone call by a research assistant to confirm the fall and to ascertain the circumstances around the fall including whether the fall resulted in any injuries, what treatment was sought.

Secondary outcome measures include:

• Dynamic balance and strength (sub-sample only)

• Physical performance (sub-sample only)

• Quality of life

• Walking behaviour

Other measures will be collected through the initial screening and baseline questionnaire and include basic demographic information, falls history, falls efficacy, self-reported levels of physical activity, walking self-efficacy and perceived neighbourhood walkability.

##### Prior to screening

###### Demographic characteristics

Demographic characteristics will be collected during initial screening, including country of birth, language spoken at home, highest level of education, current work situation, if any Government pensions/benefits are received, living situation, and total time spent in a car as a driver or passenger each week. In addition, data on any medical conditions and medication use will be collected through the medical clearance forms participants fill out prior to commencing the study (see Recruitment and Randomization).

###### Cognitive impairment

Participants' cognitive status will be determined at screening through the Short Portable Mental Status Questionnaire [29]. Respondents will be excluded from the study if they have more than three errors in the questionnaire indicating some level of cognitive impairment.

##### Study Questionnaire

The study questionnaire is designed to gather information on various factors.

###### Falls History and Falls Efficacy

Study participants will be asked to recall any falls over the past 12 months prior to being interviewed for the baseline questionnaire. Details on the number of falls, nature of fall, injuries sustained, perceived risk of falling and visits to a general practitioner will be recorded.

Confidence in avoiding a fall will be measured using the International Fear of Falling Questionnaire (FES-I). This 16-item questionnaire includes more complex activities relevant for less fragile older people when compared to the original FES questionnaire. It has been shown to have excellent reliability and construct validity [30].

###### Physical Activity

The Incidental and Planned Exercise Questionnaire (IPEQ) is a self-report questionnaire covering frequency and duration of several levels of planned and incidental physical activity in older people [31]. It assesses low, moderate and high levels of physical activities specifically designed for older people; the question and response categories accommodate both frail and active older adults ensuring the questionnaire is appropriate for use in clinical intervention trials, and it has good reliability and validity [31].

###### Quality of Life

Quality of life will be assessed using the Assessment of Quality of Life (AQoL) Mark 2. This tool comprises of 20 items selected from 6 dimensions of health: independent living, social and family, mental health, coping, pain, and sense perceptions [32]. This questionnaire has been developed based on the AQoL Mark 1 which has been shown to be a sensitive and valid measure of health-related quality of life (HRQL) in community-dwelling older people [33].

###### Walking Self-Efficacy

Walking self-efficacy will be assessed with two scales. The first scale measures behavioral self-efficacy [34]. Participants rate how confident they are in walking three days per week at a brisk pace for 10, 20, 30, 40, 50 and 60 minutes **c**ontinuously. The second scale assesses self-efficacy in regards to barriers [35]. Participants rate how confident they are to walk at least three days a week in a variety of situations. Both scales use a five-point Likert scale.

###### Neighbourhood Walkability

Neighbourhood walkability will be assessed using questions adapted from the abbreviated Neighbourhood Environment Walkability Scale (NEWS-A) [36]. This scale assesses perceived environmental attributes believed to influence physical activity and has been shown to have good reliability and validity [36,37].

##### Physical performance outcomes

The subsample of the study participants undergoing the physical performance assessments will have a home-visit arranged approximately two weeks after completing their baseline interview. Ten days before the scheduled home visit these participants will be sent an accelerometer, with detailed instructions on its use and the option of calling the research team for more information. On the testing day, the research assistant will conduct the physical performance measures with participants and collect the accelerometer.

The physical performance assessment has several components including: the Short Physical Performance Battery, quadriceps strength, lower limb reaction time, and physical activity levels. In addition participants' BMI will be measured. The physical performance assessments are undertaken in the privacy of participants' homes and are estimated to take between 20-30 minutes to complete.

###### Short Physical Performance Battery

The Short Physical Performance Battery (SPPB) measures lower limb functional status by assessing balance, gait, strength and endurance of the lower extremities. The tests include side-by-side, semi-tandem, and tandem standing tests, a timed walk, and sit-to-stand 5 repeat. The Short Physical Performance Battery is a standardized measure of lower extremity physical performance and is found to be efficient, practical, and safe to deliver in large cohorts of older adults [38,39].

###### Quadriceps Strength Test

Quadriceps strength will be assessed by seated leg extension of the dominant lower extremity, measured using a portable electronic dynamometer (Brand: CE. Model: OCS-2. Max = 60 kg, d = 20 g). The highest force achieved in three attempts is recorded [40].

###### Lower Limb Reaction Time

Lower limb reaction time will be measured through the Choice Step Reaction Time (CSRT). This test requires participants to perform quick, correctly targeted steps in response to visual cues [40]. This test has been identified as an independent and significant predictor of falls, and elucidates the roles of specific neuropsychological, sensorimotor, speed, and balance factors in the initiation of fast and appropriate step responses [41].

###### Physical Activity levels

Physical activity levels of the sub-sample of participants will be monitored using accelerometers (Actigraph GT1M, Pensacola FL USA). A sub-sample of participants, from both intervention and control groups, will be asked to wear accelerometers from the time they get out of bed until they go to sleep for 10 continuous days, timed to coincide with the physical performance measures at baseline, 3, 6 and 12-months.

###### Body mass index (BMI): Height and weight

Height will be measured in centimeters with a self-retracting construction measuring tape (max = 3 m, d = 0.5 cm). Weight will be measured in kilograms with digital weight scales (Propert Model: 3120. Max 150 kg, d = 100 g). BMI will be calculated from these measurements using the conventional formula BMI = Weight (kg)/(Height^2 ^(m^2^)).

#### Sample size

Previous falls prevention studies involving physical activity have shown a relative reduction of falls of between 20-35% [6]. Over a 12-month period it is expected that 33% of older people aged 65 years and older will fall at least once [6]. This study is powered at the alpha = 0.05 level with 80% power. A sample size of 232 per group is required to detect a relative reduction in falls of 35% (RR = 0.65) over 12-months. Adjusting the sample size to accommodate a 10% drop-out rate this study will need a sample size of 242 per group.

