**Methods/Design:**

This study uses a randomised controlled trial design.

A total of 484 older people exercising less than 120 minutes per week will be recruited through the community and health care referrals throughout Sydney and neighboring regions. All participants are randomised into either the self-managed walking program group or the health-education waiting list group using a block randomization scheme.

Outcome measures include prospective falls and falls injuries, quality of life, and physical activity levels. A subset of participants (n = 194) will also receive physical performance assessments comprising of tests of dynamic balance, strength, reaction time and lower limb functional status.

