Walking can substantially lower the risk of many chronic diseases and ameliorate the health care costs of this population [14] yet, given the above findings, its role in falls prevention remains unclear. One study found that people aged 75 years or older who were randomised to an individually prescribed home-based exercise program, which included walking, reported fewer falls than those randomised to a control group [15]. However, another study that examined the effects of walking on bone mass density in post-menopausal women found that participants in a brisk walking group had higher fall rates compared to the control group [16]. It is possible that increased walking by older adults results in greater exposure to the risk of falling (e.g., environmental hazards). This is consistent with studies that found the highest proportion of outdoor falls occur while walking [17,18].

Further, the potential of walking to improve risk factors of falls, such as balance, is also unclear. A 15-week walking program showed no significant effect on balance among sedentary, post-menopausal women [19]. On the other hand, a study which compared three different balance training programs, including walking, found that all three programs improved dynamic balance, but walking had a bigger impact on static balance [20].

Given the inconsistent evidence on the benefits of walking in the area of falls prevention, the aims of this study are to determine:

i. if a home-based walking intervention will reduce the falls rates among healthy but inactive community-dwelling older adults (65 + years) compared to no intervention (usual activity) and,

ii. whether such an intervention can improve risk factors for falls, such as balance, strength and reaction time.

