###### Analysis

All data will be analysed according to intention to treat analysis. Falls data will be compared across intervention and control groups at 12-months (i.e. 48-weeks) using a negative binomial regression model [27,28].

Outcome data obtained from the study questionnaire will be used to compare groups at 48-weeks. Falls efficacy, walking self-efficacy as well as perceived neighbourhood walkability will be analysed using the Kruskal Wallis test, a non-parametric test. Levels of physical activity and physical performance data will be analysed using regression models that will compare groups at 48-weeks using baseline values as a covariate.

A cost-effectiveness evaluation will calculate the cost of the walking program per fall prevented and a cost-utility analysis, based on the AQoL, will estimate the incremental cost-utility ratio expressed in terms of $AUD per QALY gain (or loss).

Sensitivity analyses will be conducted comparing unadjusted results and results adjusted for potential confounding variables. Potential confounding variables include age, gender, and previous falls. Data from the intervention group will also be analysed to investigate any dose-response relationships between level of walking and falls, and level of walking and physical performance.

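### The 80% power is for the proportion who fall at least once, but the planned analysis compares fall rates, and RR = 0.65 is not labelled as a rate ratio or a faller ratio

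*Protocol article*

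**What the plan says.** The Background gives the first aim as finding out "if a home-based walking intervention will reduce the falls rates among healthy but inactive community-dwelling older adults". The main outcome, under Outcome measures, is falls over the 12-month study period. Each fall is recorded on a calendar and confirmed by telephone, so the data are counts. The Analysis section states: "Falls data will be compared across intervention and control groups at 12-months (i.e. 48-weeks) using a negative binomial regression model". It names no analysis of the proportion of participants who fall.

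The Sample size section starts from a proportion: "Over a 12-month period it is expected that 33% of older people aged 65 years and older will fall at least once". It continues: "This study is powered at the alpha = 0.05 level with 80% power", and then: "A sample size of 232 per group is required to detect a relative reduction in falls of 35% (RR = 0.65) over 12-months". It cites reductions in falls of 20-35% from earlier physical activity trials. It gives no mean number of falls per person and no dispersion, and it does not say whether RR means a risk ratio or a rate ratio.

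**The concern.** A ratio of fall rates and a ratio of fallers are different effects. Some people fall more than once, so a given cut in the fall rate produces a smaller relative cut in the number of people who fall at all. A calculation built on fallers therefore does not give the power of a comparison of rates. The section describes its effect as a reduction in falls but applies 0.65 to a proportion of fallers.

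The Discussion says that a finding of no reduction in falls would change where falls-prevention resources go. How far a null result can be trusted depends on the power of the analysis actually run, and a reader cannot obtain that power from this section.

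**Working it through.** **Step 1: reproduce 232.** Inputs from the Sample size section: p1 = 0.33, RR = 0.65, alpha 0.05 (two-sided assumed, since sidedness is not stated) and 80% power. Then p2 = 0.65 × 0.33 = 0.2145 and the mean proportion is 0.27225.

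n = [1.96 √(2 × 0.27225 × 0.72775) + 0.8416 √(0.33 × 0.67 + 0.2145 × 0.7855)]² / (0.33 − 0.2145)²
= (1.2338 + 0.5253)² / 0.01334 = 231.96, so **232 per group**.

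The match is exact. Variants do not match: 249 with continuity correction, 230 with unpooled variance, 241 on the log risk ratio, 231 with the arcsine method and 183 one-sided. The calculation is for ever-fallers.

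**Step 2: carry the 33% into the planned model.** Assume negative binomial counts with mean μ and dispersion k (variance μ + kμ²). The article gives no k, so a range is shown. The control mean follows from setting the probability of no fall to 0.67:

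μ1 = (0.67^(−k) − 1)/k, and μ1 = −ln 0.67 = 0.400 at k = 0 (the Poisson limit).

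For a rate ratio R and n analysed per group:

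Var(log R) = [1/μ1 + 1/(R μ1) + 2k]/n; power = Φ(|ln R|/SE − 1.96).

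**Step 3: RR = 0.65 read as a rate ratio, n = 232.** Worked case at k = 0: the bracket is 1/0.4005 + 1/(0.65 × 0.4005) = 6.339. SE = √(6.339/232) = 0.1653, and 0.4308/0.1653 − 1.96 = 0.646, which gives power of 74%.

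| k (assumed) | μ1 | Power at 232 | n per group for 80% | Implied faller ratio | Rate ratio detectable at 80%, n = 232 |
|---|---|---|---|---|---|
| 0 | 0.400 | 74% | 268 | 0.69 | 0.63 |
| 0.5 | 0.443 | 72% | 284 | 0.72 | 0.62 |
| 1 | 0.493 | 69% | 303 | 0.73 | 0.61 |
| 2 | 0.614 | 63% | 344 | 0.77 | 0.59 |
| 3 | 0.775 | 58% | 392 | 0.80 | 0.57 |

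Simulated negative binomial fits (600 runs each) gave 74%, 71%, 63% and 56% at k = 0.5, 1, 2 and 3, close to the formula. With 33% fallers held fixed, power falls as k rises, so 74% is a ceiling that needs no value of k. Even if all 242 enrolled per group were analysed, the ceiling would be 76%.

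**Step 4: RR = 0.65 read as a faller ratio, n = 232.** Solve μ2 from 21.45% fallers in the same way, with the same k.

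| k (assumed) | Implied rate ratio | Cut in fall rate | Power at 232 |
|---|---|---|---|
| 0 | 0.60 | 40% | 85% |
| 0.5 | 0.58 | 42% | 88% |
| 1 | 0.55 | 45% | 90% |
| 2 | 0.51 | 49% | 94% |
| 3 | 0.46 | 54% | 96% |

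On this reading the planned test has more than the stated 80%, but it assumes a cut in the fall rate beyond the cited 20-35%.

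**The case against.** The strongest reply is that the calculation itself shows how the ratio was used. The only baseline is a proportion, 0.65 applied to it gives 232 exactly, and so RR was a faller ratio. On that reading the negative binomial analysis is better powered than claimed. This stands as an account of the arithmetic. It does not settle the target effect, because the same sentence speaks of a reduction in falls, the aim speaks of fall rates, and the faller reading needs a larger rate reduction than the section's own evidence range.

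A reader might infer that the plan's own inputs give 58-74% power. They do not. The article states neither a dispersion nor a mean fall rate. Only the 74% ceiling follows from the 33%, and only under the rate-ratio reading and the count model. The 58% needs an assumed k of 3; k = 4 would give 52%. The ceiling also depends on the 33%: a mean of 0.6 falls with k = 0.5 gives 82% power, but implies about 41% fallers.

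The objection that the planned test and its estimate remain valid is also correct. What is wrong is the stated power, not the analysis.

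**Conclusion.** The point holds in this form: the 232 per group and 80% power are for a comparison of ever-fallers, the aim and planned analysis concern fall rates, and the effect size is undefined between the two.

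- **Rate ratio of 0.65:** power at 232 analysed per group is at most 74%, and about 72% to 63% if k is assumed to be 0.5 to 2.
- **Faller ratio of 0.65:** power is about 85% to 96% over k = 0 to 3, for an implied rate ratio of 0.60 to 0.46.

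Both sets of figures assume negative binomial counts, a common k in the two groups, 33% control fallers and a two-sided 5% test. A reader might conclude that the trial is simply underpowered. The documents do not establish that, because the direction of the error depends on which ratio was meant. The rate reading fits the wording and the cited range better; the faller reading fits the arithmetic.

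The inflation for drop-out (232/0.9 = 258, against the stated 242) is a separate point, and none of the conclusions above rest on it.

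**What to change.** In the Sample size section, label RR = 0.65 as a rate ratio or a faller ratio. State the assumed control fall rate per person-year and the dispersion, with their source. Keep the enrolled number and restate either the power of the negative binomial test for the chosen rate ratio, or the rate ratio detectable with 80% power. With 232 analysed and 33% control fallers, the detectable ratio is about 0.63 at k = 0 and 0.62 to 0.59 over k = 0.5 to 2. A short table over that range of k would be enough. If the faller ratio was meant, also give the implied rate ratio and explain why a cut beyond the cited range is expected.

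The cost is one recalculated paragraph and possibly a less favourable stated power. Recruitment and the planned analysis do not change.

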##### Sub-sample

Sample size calculation for the sub-sample is based on outcomes of the choice step reaction time test, which is a good approximation for overall dynamic balance [41]. Based on unpublished data from Central Sydney Tai Chi trial,[27] an estimated standard deviation of 0.2 ms can be expected. A sample size of 88 participants from each group will detect an absolute difference of 10% in reaction time. Assuming a 10% drop out rate, a sample size of 97 per group will be sufficient to detect a 10% absolute difference in reaction time between groups with an alpha of 0.05 and with power of 80%.

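### The target of 242 per group does not contain the stated 10% drop-out allowance: it covers about 4% loss, and at 10% loss power on the plan's own basis is 77.5%, not 80%

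*Protocol article*

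**What the plan says.** The Sample size section sets the error rate and power ("This study is powered at the alpha = 0.05 level with 80% power") and gives the control-group assumption: "it is expected that 33% of older people aged 65 years and older will fall at least once". It then gives the number needed before any losses: "A sample size of 232 per group is required to detect a relative reduction in falls of 35% (RR = 0.65) over 12-months". The next sentence applies the drop-out allowance: "Adjusting the sample size to accommodate a 10% drop-out rate this study will need a sample size of 242 per group".

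The Methods/Design part of the Abstract carries twice that figure forward as the recruitment target: "A total of 484 older people exercising less than 120 minutes per week will be recruited".

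The Sub-sample paragraph uses the same 10% rate. It starts from 88 per group and ends: "Assuming a 10% drop out rate, a sample size of 97 per group will be sufficient".

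**The concern.** Two adjacent sentences print a base, a loss rate and a result, and the three do not agree. An allowance for 10% loss should raise 232 by a tenth or slightly more; here it rises by 10 participants, or 4.3%. The sub-sample paragraph, with the same stated rate, rises from 88 to 97, which is a full tenth.

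At stake is the justification of the recruitment target for the primary outcome. A reader would take 484 as enough to keep 80% power if one participant in ten is lost. If the allowance is missing, the trial falls below its stated power under exactly the loss it planned for. The effect assumed is already the largest in the 20–35% range that the section cites, so there is no slack there to absorb a shortfall.

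**Working it through.** **Inputs, all from the Sample size section unless noted**
- Control proportion falling at least once in 12 months: p1 = 0.33
- Relative risk 0.65, so p2 = 0.33 × 0.65 = 0.2145
- Difference d = 0.33 − 0.2145 = 0.1155; mean proportion p̄ = 0.27225
- Alpha 0.05; the section does not say one- or two-sided. Two-sided is assumed here because it reproduces the printed base
- Power 80%; equal groups (implied by the per-group figures)
- Drop-out 10%
- Sub-sample: 88 before and 97 after the same 10% (Sub-sample paragraph)

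**Step 1. Reproduce the base of 232**

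Pooled two-proportion formula without continuity correction:

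n = [1.960 × √(2p̄(1 − p̄)) + 0.8416 × √(p1(1 − p1) + p2(1 − p2))]² / d²

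- √(2 × 0.27225 × 0.72775) = √0.39626 = 0.6295
- √(0.2211 + 0.16849) = √0.38959 = 0.6242
- n = (1.2338 + 0.5253)² / 0.1155² = 3.0944 / 0.01334 = 231.96, so **232**

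This matches exactly. The base is sound, and the fault lies in the step that follows.

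**Step 2. Apply the 10% allowance**

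| Rule | Calculation | Per group | Total |
|---|---|---|---|
| Divide by the retained fraction | 232 / 0.90 = 257.8 | 258 | 516 |
| Add 10% | 232 × 1.10 = 255.2 | 256 | 512 |
| Printed | – | 242 | 484 |

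The printed figure is 14 to 16 per group, or 28 to 32 in total, below either rule. That is too much for rounding or for a choice between the two rules.

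**Step 3. What 242 does cover**
- Inflation applied: 242 / 232 = 1.043, or 4.3%
- Loss tolerated with 232 still evaluable: 1 − 232/242 = 4.1%

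**Step 4. Power at the planned loss**

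Power = Φ[(d√n − 1.2338) / 0.6242]

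| Evaluable per group | How it arises | Power |
|---|---|---|
| 242 | 242 recruited, no loss | 81.6% |
| 232 | 242 recruited, 4.1% loss | 80.0% |
| 217.8 | 242 recruited, 10% loss | 77.5% |
| 232.2 | 258 recruited, 10% loss | 80.0% |

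**Step 5. The sub-sample as a comparator**

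88 × 1.10 = 96.8, so 97: the add-10% rule. The same rule applied to 232 gives 256, so the two paragraphs treat the same stated drop-out rate differently.

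**Step 6. Could another formula rescue 242?**

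Other two-sided versions of the base give 230 (unpooled), 231 (arcsine), 241 (log relative risk) and 249 (continuity-corrected). The 241 is close to 242, but it contains no allowance for loss, whereas the text presents 242 as 232 after that allowance. No version links 232 and 10% to 242.

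**The case against.** The strongest reply accepts the arithmetic and disputes its weight. Four points deserve an answer.

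- **The loss of power is small.** It is 2.5 percentage points. On the same formula, 218 per group has 80% power for a relative risk of about 0.64 instead of 0.65. Design, outcome and conduct are untouched, and alpha, power, control proportion, relative risk and the 232 all fit together. This stands: only the last step fails.
- **77.5% is not the power of the primary analysis.** The Analysis section compares falls with a negative binomial model, while the 77.5% is for a comparison of proportions with every drop-out discarded. A count model can use partial follow-up, so its power at 484 could be higher or lower. This also stands as a limit on the figure. It does not remove the contradiction, because the section sizes the trial on the proportion falling at least once and itself treats drop-out as requiring more participants. The article gives no fall rate or dispersion from which another power could be worked out.
- **The sub-sample is not a clean benchmark.** Under the divide-by-0.90 rule, 88 becomes 97.8, so 98 and not 97. That is fair. It shows that a different rule was used there, not what the main figure should be, and it is why the shortfall is given as a range.
- **An article condenses the full protocol.** Nothing is said to be missing here. The base, the rate and the result are all printed and disagree, and no document outside the article can make 232 adjusted for 10% equal 242.

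**Conclusion.** The concern holds. The printed 242 per group does not include a 10% drop-out allowance on the printed base of 232. It covers 4.1% loss. The stated allowance calls for 256 to 258 per group (512 to 516 in total), so 484 is 28 to 32 short. With 10% loss, power on the plan's own basis is 77.5% against the stated 80%.

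The contradiction between 232, 10% and 242 rests on nothing beyond the printed figures. The power figure rests on a two-sided 5% test of two proportions (33% against 21.45%), equal groups, and drop-outs contributing nothing. It should not be read as the power of the negative binomial analysis. The practical loss is modest, but the statement that justifies the recruitment target is wrong as written.

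**What to change.** Correct the last sentence of the Sample size section in one of two ways.

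1. **Keep 484 and restate what it gives.** For the comparison of the proportions falling at least once (33% against 21.45%, two-sided 5%), 242 per group gives 80% power with up to about 4% loss, and 77.5% with 10% loss. This costs a wording change and a slightly less favourable power statement. No extra participants are needed and the Abstract stays as it is.
2. **Keep the claim of 80% power with 10% loss and change the target.** Print 258 per group, 516 in total, and change 484 in the Abstract to match. This costs 32 more participants.

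The first is enough to make the plan consistent. Whichever is chosen, state that the test is two-sided and use one inflation rule in both sample-size paragraphs. Under the divide-by-0.90 rule, the sub-sample's 97 becomes 98 per group.
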